### Statistical Analyses

As this is a pilot study, we are not statistically powered to detect the magnitude of differences we will be looking for in the full trial. Nevertheless, we will undertake similar analyses to those we will use in the full trial and regard them as exploratory in nature. First, descriptive statistics will be used to characterize the sample. All variables will be analyzed for their distribution, and relevant transformations will be applied if distributions are nonnormal. For the primary outcome, change from baseline heiQ scores will be analyzed using multiple linear regression, using the intent to treat principle. The dependent variable will be the change from baseline heiQ scores while the independent variables will be group assignment, age, sex, and any clinically relevant baseline factors identified. Change in health-related quality of life and self-efficacy questionnaire scores and differences in medication adherence scores will be modeled in the same method as the primary outcome. Predictors of hospital readmissions and mortality will be analyzed with logistic regression while a survival analysis will be used to evaluate the time until event between the 2 groups using a Cox proportional hazards regression. Group assignment, age, and sex will be a priori covariates. Clinically relevant differences in baseline factors will be included as covariates in the models. Missing values will be addressed as per the guidelines provided with the questionnaires. SPSS (IBM Corp) will be used for statistical analysis. Statistical significance will be set at *P*<.05.

An economic evaluation will also be performed alongside the pilot trial, utilizing EQ-5D-5L and health care resource use data collected during the 60-day follow-up period. A cost-consequence analysis framework will be used as the base case economic evaluation [44,45] where resource use (and associated costs) and outcomes (eg, quality-adjusted life years [QALYs] generated from EQ-5D-5L responses) within the 2 study groups are listed, separately, in a disaggregated format. This type of evaluation makes no attempt to combine costs and effects into a single outcome measure (such as a cost-per-QALY ratio) and has particular value in aiding transparency. Canadian guidelines for the conduct and reporting of economic evaluations will be followed; publication of updated Canadian guidelines is expected in early 2017 [46].

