### Study Outcomes

The primary outcome is the change in self-management between the 2 groups as measured by the heiQ. The heiQ comprises 40 questions and measures 8 domains that are indicators of effective self-management programs: positive and active engagement in life (5 questions), health-directed behavior (4 questions), skill and technique acquisition (4 questions), constructive attitudes and approaches (5 questions), self-monitoring and insight (6 questions), health service navigation (5 questions), social integration and support (5 questions), and emotional well-being (6 questions). Items are scored on a Likert scale from 1 to 4. The heiQ was developed using item response theory and structural equation modeling and the subscales have acceptable to high internal consistency (Cronbach alphas ranging from .70-.86, depending on the domain) [30]. The heiQ has been used in a broad range of patient education programs including ehealth settings and with CVD patients [35]. The heiQ will be measured at both the baseline and follow-up sessions.

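### Baseline heiQ is not a pre-specified covariate in the primary change-score model, so whether the estimate is adjusted for it depends on the observed data; fixing it in advance would add precision at no cost

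*Protocol article*

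**What the plan says.** The Study Outcomes section defines the endpoint: "The primary outcome is the change in self-management between the 2 groups as measured by the heiQ". It also confirms that the baseline value will exist: "The heiQ will be measured at both the baseline and follow-up sessions". The Randomization and Baseline Assessment sections place the baseline questionnaires, heiQ included, before allocation.

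The Statistical Analyses section then sets out the model. On the outcome: "The dependent variable will be the change from baseline heiQ scores". On the predictors: "the independent variables will be group assignment, age, sex, and any clinically relevant baseline factors identified". Later in the same paragraph come two further rules: "Group assignment, age, and sex will be a priori covariates", and "Clinically relevant differences in baseline factors will be included as covariates in the models".

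The primary model is carried over to other scales: "Change in health-related quality of life and self-efficacy questionnaire scores and differences in medication adherence scores will be modeled in the same method". The baseline heiQ score is not named as a covariate anywhere in the article.

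**The concern.** A change score with no baseline term fixes the coefficient of the baseline score at 1. When baseline and follow-up are imperfectly correlated and their SDs are similar, the true slope is below 1, so subtracting the whole baseline over-corrects. This has two consequences:

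- The treatment estimate carries variance that a baseline term would remove.
- If one arm starts higher by chance, regression to the mean pulls the estimate against that arm.

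Randomisation is stratified by sex only, so the design does not balance baseline heiQ. With 76 participants, a chance difference of some size is to be expected.

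The open wording on baseline factors adds a separate difficulty. It allows baseline heiQ into the model, but gives no threshold and no commitment made before the data are seen. Whether the primary estimate is adjusted for its strongest likely predictor would then depend on inspecting the baseline table. The article says that the pilot analyses resemble those intended for the full trial, so the model form is worth settling now.

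**Working it through.** **Inputs from the article.** The sample is 76 with 1:1 allocation, hence 38 per arm (Sample Size, Randomization). The 76 is a recruitment figure, not a power calculation. It reproduces closely: 750 discharges a year × 0.5 year × 0.40 eligible × 0.50 consenting = 75.

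**Assumptions.** The article gives neither an SD nor a baseline/follow-up correlation r. I take equal baseline and follow-up SDs, work in SD units, assume all 76 complete follow-up, and let r run from 0.3 to 0.8.

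**Formulas**, with n = 38 per arm:

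- SE of the change-score difference = √[2 × 2(1 − r)/n]
- SE of the baseline-adjusted difference = √[2(1 − r²)/n]
- Variance ratio, adjusted to change score = (1 + r)/2
- SE of the chance baseline difference = √(2/38) = 0.229 SD
- Given a baseline difference D (intervention minus control), the unadjusted estimate is shifted by −(1 − r)D

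Worked at r = 0.5: change-score SE = √(2 × 1.0/38) = 0.229, adjusted SE = √(2 × 0.75/38) = 0.199, variance ratio 0.75, and shift at D = 0.229 of −0.5 × 0.229 = −0.11 SD.

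| r | SE, change score | SE, adjusted | SE reduction | Shift at D = 0.229 |
|---|---|---|---|---|
| 0.3 | 0.271 | 0.219 | 19% | −0.16 |
| 0.5 | 0.229 | 0.199 | 13% | −0.11 |
| 0.7 | 0.178 | 0.164 | 8% | −0.07 |
| 0.8 | 0.145 | 0.138 | 5% | −0.05 |

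Equivalently, the change-score analysis of 76 patients is worth an adjusted analysis of 76 × (1 + r)/2, or about 49, 57, 65 and 68 patients.

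**Simulation check.** For each of three values of r, 8,000 trials of 76 were simulated with age and sex in the model and no treatment effect. Three strategies were compared: baseline never included, baseline always included, and baseline included only if the observed arm difference exceeded 0.25 SD. The 0.25 SD trigger is an assumed reading of the open clause, since the article gives none.

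| r | SD of estimate: never | trigger | always |
|---|---|---|---|
| 0.3 | 0.278 | 0.238 | 0.224 |
| 0.5 | 0.237 | 0.215 | 0.206 |
| 0.7 | 0.182 | 0.173 | 0.169 |

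The share of the gain that the trigger recovers is (0.278 − 0.238)/(0.278 − 0.224) = 74%, (0.237 − 0.215)/(0.237 − 0.206) = 71%, and (0.182 − 0.173)/(0.182 − 0.169) = 69%.

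In trials where the intervention arm started more than 0.229 SD higher (mean imbalance about 0.35 SD), the average bias was:

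- never included: −0.25, −0.18 and −0.10 SD at r = 0.3, 0.5 and 0.7
- trigger: −0.03, −0.02 and about 0
- always included: about 0 throughout

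With baseline in the model, using change or follow-up score as the outcome gave the same treatment effect to rounding error.

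**The case against.** The strongest reply is that the article does not exclude baseline heiQ. It is a baseline factor, it is an obvious candidate under both open clauses, and the second clause is aimed at baseline differences between groups. This stands. A reader might infer that the model is to be fitted without baseline heiQ, but the text supports only that it is not pre-specified. Under the assumed trigger, about 70% of the gain and most of the conditional bias are already dealt with. What the clause does not do is secure the rest of the precision or fix the model before the data are seen.

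It is also fair to say that the method is valid. A reader might infer that the treatment estimate is biased outright. It is not: over repeated randomisations the change-score estimate is unbiased, and the bias arises only conditional on the imbalance that occurs. The size of the gain rests on an unknown r and is small at 0.7 to 0.8.

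Two further inferences go beyond the text:

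- That QALYs will be compared without adjustment for baseline utility. The economic paragraph says only that costs and outcomes are listed by group and that Canadian guidelines will be followed; it leaves adjustment open.
- That this estimate and its SD will set the size of the larger trial. The article says only that the results will inform that trial.

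Finally, an unseen analysis plan may give a fuller covariate list. That does not remove the point, because the article itself states which covariates are a priori, and baseline heiQ is not among them.

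**Conclusion.** The point holds as one of pre-specification and efficiency, with moderate severity. The a priori covariates are group, age and sex. Baseline heiQ is available for everyone randomised, yet it can enter only by a choice made after the baseline data are seen.

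Fixed adjustment would cut the standard error by roughly 5% to 19% over r = 0.8 to 0.3, and would remove the shift that a chance imbalance otherwise leaves in the estimate. Those figures assume 38 per arm, no loss to follow-up, equal SDs and a correlation the documents do not give. They are measured against a model in which the open clause is never used; if it is used, the remaining gain is smaller. The analyses are declared exploratory and the sample was not set to detect group differences, so nothing here invalidates the pilot.

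**What to change.** In the Statistical Analyses section, name the baseline score of the same scale as a fixed a priori covariate alongside group, age and sex, to be included whatever the observed imbalance. Apply this to the heiQ model, separately for each domain analysed, and to the EQ-5D-5L and cardiac self-efficacy change models, each with its own baseline. The medication adherence scale is measured only at follow-up, so it has no baseline to add. Change can stay as the outcome.

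The cost is one sentence and one degree of freedom per model. No new data are needed, and the planned linear regression in SPSS accommodates it.

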## Introduction

### Background

Cardiovascular disease (CVD) is one of the leading causes for hospitalization and death in Western countries [1,2]. Acute coronary syndrome (ACS) includes the diagnoses of acute myocardial infarction (AMI) and unstable angina. AMIs are the second most common reason for inpatient admissions in Canada (excluding giving birth), with over 60,000 cases [3] while ACS was the primary or secondary cause of over 1.1 million unique hospital admissions in the United States in 2010 [4]. Approximately 60% of these admissions were due to AMIs, making AMIs a leading cause for inpatient admissions [4,5]. The initial period following discharge is the highest risk for readmission, with 14% of AMI patients having an urgent readmission within 15 days of discharge and 20% of patients being readmitted by 30 days [6]. In the United States, Dharmarajan et al [7] found that AMI patients’ daily change in risk of readmission has declined by 95% by day 38 postdischarge. In Canada, the median days until readmission in ACS patients was 23 (interquartile range: 5 to 41 days) [8]. Readmissions are of concern because of the impact on patient quality of life [9] and the cost to the health care system, which has been estimated at $1 billion in the United States in 2013 [10,11].

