### Sample Size

A convenience sample of 76 participants will be enrolled in the study. This sample size is based on the feasibility of recruitment over a 6-month time period and is not determined in order to be able to detect between-group differences. Approximately 750 unique ACS patients were discharged from the target hospital during the 2012/2013 fiscal year. In a preliminary feasibility survey of patients, 14 of 28 had mobile phones with texting capabilities. Assuming 40% are eligible and 50% agree to participate [32], we expect approximately 76 patients will agree to participate over 6 months of recruiting.

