### Randomization

After discharge and once the baseline assessment has been completed, participants will be randomized to receive either usual care or usual care plus the 60-day text messaging program (Txt2Prevent) using a 1:1 allocation ratio. To minimize bias, randomization will be conducted by a research assistant who is not involved in either the recruitment or data collection phases. This research assistant will use a Web-based randomization service developed through an independent research center. To ensure balance between the groups, the randomization will be stratified by sex and use block randomization with variable block sizes. The randomization research assistant will register participants for the TxT2Prevent intervention, when appropriate, and then contact all participants by phone to inform them of their group assignment. The start date for participants in the Txt2Prevent program will be documented. A letter will also be sent to all study participants’ primary care providers informing them that their patient has been enrolled in the study. Primary care providers will be identified by the participant. The primary care providers’ addresses will be obtained online from the registry maintained by the provincial licensing and regulatory body for physicians. Participants will be told to contact the research assistant who performs the randomization during the course of the study if they have any questions. Participants will be aware that the text messaging program is the intervention of interest as it is being compared to usual care.

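### Covariate-adjusted logistic and Cox models are planned for 60-day mortality in 76 patients, where the group effect will often have no finite estimate

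*Protocol article*

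**What the plan says.** The Study Objectives list all-cause and cardiovascular readmission and mortality among the secondary outcomes. For these events the Statistical Analyses section states: "Predictors of hospital readmissions and mortality will be analyzed with logistic regression". The same sentence adds a Cox proportional hazards model to compare time to event between the two groups. On covariates it says: "Group assignment, age, and sex will be a priori covariates". It then adds, without limiting the number, baseline factors that show clinically relevant differences. The significance level is P<.05.

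On size, the Sample Size section says: "A convenience sample of 76 participants will be enrolled in the study". It adds that this number "is not determined in order to be able to detect between-group differences". Follow-up is 60 days from randomization (Follow-up Assessment). Statistical Analyses says that the pilot is not powered, that its analyses resemble those of the full trial, and that they are exploratory.

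The article gives no mortality rate and no expected number of deaths. Its only event rates are background readmission figures for patients with myocardial infarction, including "20% of patients being readmitted by 30 days".

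**The concern.** A regression model for a binary or time-to-event outcome needs events in both arms before it can estimate a group effect. With a few deaths at most, one arm may well have none, and the trial may have none at all. In the first case the likelihood keeps rising as the group coefficient goes to plus or minus infinity (separation in logistic regression, monotone likelihood in Cox regression). In the second there is nothing to fit. Software then either stops or prints an arbitrary very large or very small ratio with an enormous standard error.

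This is a stated method that may not work on the stated sample, not a detail left to another document. A mortality ratio of that kind tells the reader nothing. It would also take the place of the one informative summary, which is how many patients died in each arm. The results are meant to inform a larger trial, so that summary should be given in a usable form.

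**Working it through.** **Inputs.** The sample is 76 (Sample Size), randomized "using a 1:1 allocation ratio", so I take 38 per arm. Follow-up is 60 days. The fixed model terms are group, age and sex. The 60-day mortality p is not in the document, so I show 1% to 8% as an assumed range.

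**The plan's own figure.** The sample size rests on recruitment: about 750 discharges a year, half a year, 40% eligible, 50% consenting. 750 × 0.5 × 0.40 × 0.50 = 75, which agrees with the stated 76. It involves no event rate.

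**Mortality, group term.** Take the same true risk p in both arms. One arm has no deaths with probability (1−p)^38. At least one arm has none with probability 1 − (1 − (1−p)^38)². For p = 2%: 0.98^38 = 0.464, and 1 − (1 − 0.464)² = 0.713.

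| Assumed 60-day mortality | Expected deaths (76p) | No deaths in the trial, (1−p)^76 | At least one arm with no deaths |
|---|---|---|---|
| 1% | 0.8 | 47% | 90% |
| 2% | 1.5 | 22% | 71% |
| 3% | 2.3 | 10% | 53% |
| 4% | 3.0 | 4% | 38% |
| 5% | 3.8 | 2% | 26% |
| 8% | 6.1 | 0.2% | 8% |

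In every trial counted in the last column, the group coefficient has no finite estimate. Adding age and sex cannot repair that. The Cox model fails under the same condition.

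**Mortality, full model.** Age and sex bring further ways to fail, for example when all deaths are in one sex. A separation check on 500 simulated trials per setting used the group, age and sex logistic model, with 25% or 50% women and an age odds ratio of 1 or 2 per 10 years. The model had no maximum-likelihood fit in 93–96% of trials at 1% mortality, 79–87% at 2%, 66–74% at 3%, 37–53% at 5% and 13–28% at 8%. These figures are for the model as a whole, so in some of these trials the group term alone would still be finite.

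**Cardiovascular mortality.** Cardiovascular deaths are a subset of all deaths, so each probability is at least as high.

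**Readmission.** If the 20% background rate applied, events would number 76 × 0.20 = 15.2, or 15.2/3 = 5.1 per fixed coefficient. The same separation check found no fit in only 0–3% of trials, so this model can be estimated. It is imprecise: the unadjusted large-sample standard error of the log odds ratio is √(2/(38 × 0.20 × 0.80)) = 0.57. The upper 95% limit is then exp(2 × 1.96 × 0.574) ≈ 9.5 times the lower. The 20% is a 30-day rate in myocardial infarction, while the trial enrols acute coronary syndrome and follows for 60 days, so 15 events is only a guide. Rates of 14% to 30% would give 11 to 23 events.

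**The case against.** The best defence is that these are secondary outcomes of a pilot. The article says that it is not powered and that the analyses are exploratory rehearsals for the full trial, and a fallback for sparse data often sits in an analysis plan that is not shown. The mortality rate is also assumed. At about 6% to 8% or more, the group term would usually be estimable.

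Much of this stands, and it sets the severity. It does not remove the point. Low power gives a wide but valid interval, whereas separation gives no finite estimate. The article also names mortality explicitly for these models; it does not leave the method open.

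The documents do not support several stronger readings that a reader might infer:

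- That the readmission model fails too. At about 15 events it can be fitted, and its imprecision is already conceded.
- That eight separate models are specified. The all-cause and cardiovascular split comes from the objectives; Statistical Analyses does not say that each version gets both models.
- That the Cox model merely repeats the logistic one. It uses event timing and handles censoring, and the article gives the two different purposes.
- That a separated fit would look like an efficacy or safety signal. The Wald standard error becomes huge and the P value approaches 1, so the likelier result is an uninterpretable ratio.
- That event ratios will size the full trial. The article says only that results will inform it.

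**Conclusion.** The point holds for mortality. As written, the logistic and Cox models would give no finite group effect in more than half of trials if 60-day mortality is about 3% or less, and in about a quarter at 5%. The full adjusted logistic model does worse. The calculation assumes 38 per arm, complete follow-up and no true difference. The mortality rate is assumed, so that the models will usually fail is conditional on that range and is not established by the document. For readmission, the remaining weakness is that an open-ended set of covariates, chosen because they look imbalanced, would be added to a model with about five events per fixed coefficient. Severity is modest: the primary self-management analysis and the feasibility and acceptability aims are untouched.

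**What to change.** - **Mortality.** Remove all-cause and cardiovascular death from the logistic and Cox models. Report the number of deaths and of cardiovascular deaths by arm, with exact 95% confidence intervals and no significance claim. For example, 0 of 38 gives 0% to 1 − 0.025^(1/38) = 9.3%, which states plainly what the trial can exclude.
- **Readmission.** Keep the model, but fix its terms as group, age and sex and use Firth-penalised estimation. Add no covariates on the strength of observed baseline imbalance. Report the estimate with its 95% confidence interval beside the risk in each arm.

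The cost is small: there would be no adjusted mortality ratio to report. If the SPSS version in use lacks Firth estimation, another package must be named. The article reports data collection as complete, so the change needs no new data. It should be recorded in the analysis plan before the outcomes are analysed by arm or, failing that, reported as a change from the published protocol.

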### Assessments

#### Baseline Assessment

When possible, the baseline assessment will be done as a face-to-face session prior to hospital discharge. In situations where the baseline assessment cannot be completed prior to discharge, it will be completed by phone or through an online survey within 7 days of discharge. The assessment will consist of the heiQ, EQ-5D-5L, and Cardiac Self-Efficacy questionnaires. Participants will also be asked demographic questions (age, sex, marital status, geographic location, employment status, education, and household income) and questions about their mobile phone (frequency of use, texting frequency, need for help or support, confidence in using, type of mobile phone, and ownership). Medical history (reason for admission, comorbidities, previous cardiac events, and smoking status) will also be obtained through a combination of self-report and medical record review. Trained assessors will be blinded as randomization will not occur until after the baseline assessment.

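### Beyond age and sex, covariates enter the models because the arms happen to differ at baseline, not because they predict outcome, and the baseline score is not named

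*Protocol article*

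**What the plan says.** All references are to the protocol article.

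- **Covariates fixed in advance** (Statistical Analyses): "Group assignment, age, and sex will be a priori covariates".
- **Further covariates, all models** (the next sentence): "Clinically relevant differences in baseline factors will be included as covariates in the models".
- **Primary model** (change from baseline heiQ, linear regression): "the independent variables will be group assignment, age, sex, and any clinically relevant baseline factors identified". Baseline heiQ is not named.
- **Other questionnaire outcomes:** change in quality of life, change in self-efficacy, and medication adherence "will be modeled in the same method as the primary outcome".
- **Event outcomes:** "Predictors of hospital readmissions and mortality will be analyzed with logistic regression", with a Cox model for time to event.
- **Pool of candidates** (Baseline Assessment): "age, sex, marital status, geographic location, employment status, education, and household income"; six items on mobile phone use and ownership; and "reason for admission, comorbidities, previous cardiac events, and smoking status".

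The heiQ, EQ-5D-5L and cardiac self-efficacy scale are measured at baseline and follow-up. Medication adherence is measured at follow-up only (Study Outcomes).

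**The concern.** The rule on differences stands directly after the a priori list and in contrast to it. Differences between arms can be seen only after randomisation. With 1:1 allocation through an independent web-based service, they arise by chance. Chance imbalance is a poor reason to adjust. What makes a covariate useful is how well it predicts the outcome. A rule keyed to imbalance can admit a variable that predicts nothing and pass over one that predicts a great deal.

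The content of the adjusted model, and so the estimate, then depends on a later choice. The best candidate is also easy to miss: a change score does not by itself adjust for the baseline score, and that score is collected for three of the four questionnaire outcomes.

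This is more than a list left to an analysis plan. The article states a principle of selection, and a plan that followed it would inherit the weakness.

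**Working it through.** **Inputs from the article.** N = 76, 1:1, so 38 per arm; significance at P<.05 (taken as two-sided). The sample size rests on recruitment and reproduces: 750/2 × 0.40 × 0.50 = 75, against 76 stated. The plan gives no effect size, power or standard error to reproduce.

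**1. How often chance differences appear.** The SE of a standardised baseline difference is √(2/38) = 0.229. For one factor, P(|difference| ≥ 0.3 SD) = 0.191 and P(|difference| ≥ 0.5 SD) = 0.029. For k independent factors, the chance of at least one is 1 − (1 − p)^k. The article gives no threshold, so both the threshold and k are assumptions:

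| Candidates beyond age and sex | ≥ 0.3 SD | ≥ 0.5 SD |
|---|---|---|
| 15 (5 demographic, 6 phone, 4 medical history) | 0.96 | 0.36 |
| 9 (phone items left out) | 0.85 | 0.23 |
| 4 (medical history only) | 0.57 | 0.11 |

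Depending on the reading, the rule would be triggered rarely or nearly always.

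**2. What an imbalance rule does.** Simulation: 5,000 null trials per row; 12 candidates, 3 of them prognostic with joint R² as shown; age and sex (together R² 0.08) always in the model; linear model. Entries are the empirical SD of the group effect, in outcome SDs.

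| Joint R² | Age and sex only | Plus factors with imbalance > 0.25 SD | Plus the 3 prognostic factors, prespecified |
|---|---|---|---|
| 0 | 0.225 | 0.240 | 0.230 |
| 0.2 | 0.222 | 0.219 | 0.199 |
| 0.4 | 0.226 | 0.198 | 0.172 |

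- *Precision.* The imbalance rule gains something when the imbalanced factors are prognostic, but captures only part of what prespecification would. At R² = 0.4 the gain is 0.226 − 0.198 = 0.028 of an available 0.226 − 0.172 = 0.054, about half. At R² = 0.2 it is 0.003 of 0.023.
- *Reported SE.* The mean model SE under the rule is 0.237, 0.229 and 0.222, no real improvement on 0.222, 0.222 and 0.223 with age and sex only.
- *Type I error, fixed rule.* 5.1%, 3.8% and 3.0%: at or below nominal.
- *Type I error, most favourable of 5 plausible covariate sets reported.* 7.6%, 7.9% and 8.1%. A second simulation (4,000 trials, 15 candidates with coefficient 0.1, baseline correlation 0.5) gave 8.7% for the smallest p-value across its candidate models.

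**3. What the baseline score would add.** In that second simulation the SD of the group effect was 0.238 for the change score with group, age and sex; 0.242 after adding imbalanced factors; and 0.210 with the baseline score as a covariate. The imbalance rule itself therefore cost only 0.004. The move from 0.24 to 0.21 comes from the baseline score.

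A closed form, ignoring other covariates, shows the dependence on the assumed correlation r. The SE for the change score is 0.229 × √(2(1 − r)); with baseline adjustment it is 0.229 × √(1 − r²).

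| r | Change score | Baseline-adjusted | Reduction |
|---|---|---|---|
| 0.3 | 0.271 | 0.219 | 19% |
| 0.5 | 0.229 | 0.199 | 13% |
| 0.7 | 0.178 | 0.164 | 8% |

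The simulated reduction at r = 0.5 is 1 − 0.210/0.238 = 12%, in line with this.

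**The case against.** The case for leaving the text alone has five parts.

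- **Age and sex are prespecified.** True. A reader might infer that every covariate is picked after the fact; the article says otherwise, and only the additional ones are affected.
- **The rule does not inflate false positives.** True of a rule fixed in advance. A reader might infer that the plan as written carries a type I error of 8% to 9%. It does not: that figure needs someone to choose among adjusted models, which the article nowhere proposes. It also states nothing that would prevent it.
- **Imbalance-based adjustment can help precision.** True where the imbalanced factors are prognostic, so a claim of no gain would be wrong. Nor does the document support saying that the rule will almost always be triggered, since that needs a threshold of about 0.3 SD and a wide pool of candidates.
- **A condensed article may leave detail to a fuller document.** Fair for the list, threshold and timing, and none of these is held against it. The primary-model phrase, "any clinically relevant baseline factors identified", can also be read as selection on clinical relevance alone, and it does not bar baseline heiQ. The separate sentence on differences, however, applies to the models generally and sets the principle itself.
- **This is an unpowered, exploratory pilot.** True, and it limits the consequence. The same section nevertheless says that similar analyses will be used in the full trial.

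**Conclusion.** The point holds in a limited form. Beyond age and sex, the article selects covariates on observed differences between arms, which randomisation makes chance. The adjusted effect therefore depends on a post-randomisation choice not based on prognostic value, and the baseline score is not named for the outcomes that have one.

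The gain forgone by not adjusting for the baseline score is about 0.03 SD in the standard error (0.24 to 0.21) at an assumed correlation of 0.5, smaller if the correlation is higher and larger if it is lower. The simulations are illustrative: they use independent, normally distributed covariates and a linear model, so they do not speak to the logistic and Cox models. Because the analyses are declared exploratory, what is affected is the precision and credibility of the pilot estimate and the approach carried into the larger trial. No confirmatory conclusion rests on it.

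**What to change.** In Statistical Analyses:

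1. Delete the sentence that adds covariates according to baseline differences, and the open-ended phrase in the primary model.
2. For heiQ, EQ-5D-5L and cardiac self-efficacy, prespecify the baseline value of the outcome, age and sex. The dependent variable can stay as change: with the baseline value in the model, the group coefficient is the same as for the follow-up score.
3. For medication adherence, which has no baseline measure, and for the logistic and Cox models, use age and sex only.
4. Present baseline differences descriptively.
5. Label any model with further covariates as a sensitivity analysis, with the covariates chosen for prognostic relevance without sight of outcomes by arm.

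The cost is a few sentences and no new data. The article reports data collection as complete by January 2017, so for the pilot the choice has to be recorded before outcomes are viewed by arm. If they have already been viewed, report the model above beside the one used and say when each was chosen. The full trial's plan can adopt the wording from the start.
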